**Sample size calculation**

The adequate sample size for all objectives is calculated using openepi version 3 software. The sample size needed to estimate the utilization of MHS is calculated assuming the anticipated utilization of ANC (74%), births attended in an HF (48%), and PNC (34%) according to the report of 2019 Mini EDHS[[29](#_ENREF_29)], the margin of error of 5%, 95% confidence interval, 1.31 design effect. Based on the above information, the estimated sample size is 392 (ANC), 508 (births attended in a health facility), and 457 (PNC). The sample size needed for identifying the predictors associated with MHSU is calculated considering variables significantly associated with MHSU based on previous studies done in Northern Ethiopia [7], in rural Haramaya district, Eastern Ethiopia [10], and in Northwest Ethiopia [11]. For all calculations, power was set at 80%, level of confidence at 5%, and the ratio of unexposed-to-exposed were assumed to be 1. Hence, the sample size of 1,104 obtained from the second objective will be utilized due to it is the maximum sample size assessed and would be adequate to assess all objectives of this study. The minimum required sample size for the qualitative study will be determined according to the recommendation of Morse and Creswell for Phenomenological studies (20 in-depth interviews, 9 focus group discussions, and 20 key informant interviews) [[30](#_ENREF_30)]. The minimum required sample size for the third and fourth objectives is calculated based on the following considerations. Due to the lack of the previous cRCT on the same topic, assumptions on the proportion of women with knowledge on ODS in the control and intervention arms were taken from a previous quasi-experimental study. The proportion before the intervention was taken as the proportion in the control arm and the proportion after the intervention as the proportion in the intervention arm. Accordingly, P1 = 45.7% (proportion of women’s knowledge regarding ODS during pregnancy) in the control group, P2= 62.9% (proportion of women’s knowledge regarding ODS during pregnancy in the intervention arm) [[14](#_ENREF_14)], 95% CI, and 80% power. According to the above considerations, the estimated effective sample size for individual-based randomization is 286. For this objective, the sample size is adjusted to non-response rate (NRR) by dividing the initial sample size by the anticipated response rate. In case of knowledge regarding ODS during pregnancy, the adjusted sample size to NRR is 286/1 = 286.The minimum required number of clusters is computed by multiplying the effective sample size and ICC factors for both groups [28]. We received the typical value of ICC factor of 0.01 from range values (0.01 to 0.05) based on the existing recommendation [26]. Consequently, the minimum needed cluster number is 329*0.01 = 3.29 for both groups. Nevertheless, to maintain the sufficiency of the cluster and to have adequate power [26, 28], 12 clusters (*12 kebeles*) will be included in this study. To account for the effect of the cluster, the effective sample size is multiplied by a VIF of 1.26. The VIF is calculated with the assumption of an equal cluster size of 27 study subjects from 12 clusters (*kebeles*). Using ICC value of 0.01, (VIF = 1+ [(n-1) ICC]), where ‘n’ is the average cluster size [28]. Thus, the final estimated sample size is 360 (180 in the intervention arm and 180 in the control arm). However, the sample size calculated for the fourth objective which is designed to evaluate the effect of the intervention on MHSU is 1,126 (i.e., larger). Hence, the sample size of 1,126 obtained from the fourth objective will be utilized for this objective as well as it would be maximum or representatives of the sample for both objectives.

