**Study design**

A community-based cross-sectional study, phenomenological qualitative study, and parallel-group Cluster Randomized Controlled Trial (CRCT) will be used to address the objectives of the current study. The study is a 2 arm CRCT, with every cluster being *kebeles* located in the Dale and Wonsho districts of Sidama region, Ethiopia. The hallmark of this design is each cluster remains in the arm it was randomly assigned to during the course of the whole study period. Thus, all study subjects are randomly assigned into a group and all the study subjects in the assigned group obtain or do not obtain an intervention.

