**Statistical data analysis**

Data will be entered into Epidata version 3.1 and exported to the Statistical Package for Social Science (SPSS) version 25 and Stata version 14 for further processing and analysis. During the analysis, all quantitative variables will be handled by recoding, calculations, and categorizations before carrying out the main analysis. Descriptive analyses will be carried out to get descriptive measures for the important variables of interest. The descriptive statistic techniques will be utilized for the data organization and presentation. All continuous data will be checked for the normal distribution. If approximately normal distributed the mean and SD will be reported. The missing data will be handled by using multiple imputation methods. The Principal Component Analysis (PCA) will be carried out for the computation of the wealth index. The effect of clustering will be checked by using an Intra-Cluster Correlation Coefficient (ICC) value. The multilevel analysis will be considered if the calculated value of ICC is greater than 5%. Before conducting a multilevel analysis, we will decide whether or not the multilevel model is required by doing a random intercept model. This model offers data regarding ICC which is utilized to determine whether a multilevel model is required or not. If the chi-square test is significant or the ICC value is greater than 5%, the multilevel analysis model is mandatory to consider. Both bi-variable and multivariable analyses using generalized mixed models with random effects will be carried out. The Generalized Estimated Equations (GEE) or multilevel regression models will be utilized to adjust for between and within-cluster variation for adjusted analysis. Those variables with p-values < 0.25 on the bi-variable analysis model will be included in a multivariable regression model to find out predictors independently associated with MHSU adjusting for other variables in the model. The candidate variables will be entered into the multivariable regression model using the ENTER regression method. The basic assumptions of generalized mixed models will be tested before proceeding with the analysis. The stratified and multivariable analyses will be used to control for the potential confounding variables. Effect modification will be examined using stratification and entering effect modifiers into the multivariable analysis model one at a moment. Multicollinearity among the independent variables will be also evaluated using a multiple linear regression model. The variance inflation factor (VIF) < 10 and tolerance statistics > 0.1 will be used to declare the absence of multicollinearity. The presence and strength of a statistically significant association between MHSU and the independent variables will be assessed using adjusted odds ratios (AORs) with a 95% CI. A statistically significant association between the variables of interest will be confirmed when the 95% CI of the AORs did not contain 1. All analyses of the study will be carried out using a 95% CI or 5% level of significance. Though, a statistical significance level will be adjusted to account for the effect of multiple comparisons problem using the Bonferroni corrections methods. The adjusted level of significance is computed by dividing the preset level of significance by the number of statistical tests conducted (outcome variables). In our case, the adjusted level of significance is 0.05/3 = 0.017. Thus, a statistically significant association will be declared when p-value less than 0.017. After the finish of the qualitative data collection, the tape-recorded data will be transcribed verbatim of the local language and translated to English. The coding and analysis of the qualitative data will be done using the thematic content analysis technique by Atlas-Ti software and presented in narratives. A paired t-test will be utilized to measure the mean change from baseline for both groups (intervention and control) groups. Then, an independent t-test will be utilized to compare the mean change of women’s knowledge regarding ODS and BPCR practice scores and MHSU for interventional groups against the mean change of the control group as effect size. To assess the effect of HEI on maternal knowledge regarding ODS and BPCR practice scores and MHSU, an intention-to-treat analysis will be done to compare outcomes between the two groups.

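### The sample size uses normal quantiles times a VIF with no allowance for only 12 kebeles (10 degrees of freedom), so the method shown does not deliver 80% power; this matters for MHSU, not for knowledge

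*Protocol*

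**What the plan says.** In the Protocol, Sample size calculation, the trial part opens with "The minimum required sample size for the third and fourth objectives is calculated based on the following considerations". The worked example is knowledge of obstetric danger signs: 45.7% in control, 62.9% under intervention, "95% CI, and 80% power. According to the above considerations, the estimated effective sample size for individual-based randomization is 286". No non-response is added. The figure is multiplied by a VIF of 1.26 (ICC 0.01, 27 women per kebele) to give 360.

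A rule of thumb in the same section asks for about 3.3 clusters. The text then goes on: "Nevertheless, to maintain the sufficiency of the cluster and to have adequate power", and takes 12 kebeles. There is no degrees-of-freedom or t correction.

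The 360 is then replaced by 1,126, the figure for objective 4 (MHSU), which serves both objectives. The flow diagram shows 563 per arm. The rates, effect, ICC and VIF behind 1,126 are not given.

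Study design makes the kebele the unit of randomisation: "The hallmark of this design is each cluster remains in the arm it was randomly assigned to during the course of the whole study period". Statistical data analysis states "All analyses of the study will be carried out using a 95% CI or 5% level of significance", and later "the adjusted level of significance is 0.05/3 = 0.017".

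**The concern.** A design effect answers one question: how much larger is the variance because women in a kebele resemble each other? It leaves a second one open: how well is that variance known? With 6 kebeles per arm, a comparison that holds the 5% level has 12 - 2 = 10 df and a critical value of 2.228, not 1.960. Keeping 1.960 would preserve nominal power only by letting the true level rise to about 8% (the two-sided tail of t with 10 df beyond 1.960 is 0.078).

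MHSU is what the study aims to improve, and it is the outcome with no visible margin in the sample size. A null MHSU result would be read as coming from a trial with a 20% chance of missing the planned effect, when that chance may be 25-29%.

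**Working it through.** **Inputs.** From the Protocol: P1 = 0.457, P2 = 0.629 (difference 0.172), two-sided 5%, 80% power, ICC 0.01, 12 kebeles, VIF 1.26, N = 360 and then 1,126. Assumed: 6 kebeles per arm, equal sizes.

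**1. Reproduce the plan's figures.**
- Two-proportion formula with normal quantiles: n = [1.960 × √(2 × 0.543 × 0.457) + 0.842 × √(0.457 × 0.543 + 0.629 × 0.371)]² / 0.172² = (1.965 / 0.172)² = 130.5, so 131 per arm, 262 in all.
- With continuity correction: n' = (130.5 / 4) × [1 + √(1 + 4 / (130.5 × 0.172))]² = 141.9, so 142 per arm, 284 in all. The Protocol has 286, a difference of 2. The uncorrected 262 does not match. So 286 comes from normal quantiles, most likely with continuity correction.
- VIF = 1 + 26 × 0.01 = 1.26, and 286 × 1.26 = 360.4. The 360 is reproduced.

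**2. General cost of 10 df.** A design at exactly 80% by normal quantiles has noncentrality 1.960 + 0.842 = 2.802. Under the noncentral t with 10 df, power is 71.4% at 5%. At 0.05/3 it is 50%, against 66% by normal quantiles. To reach 80% with 10 df at 5% the noncentrality must be 3.110. That is a ratio of 1.11 in the detectable difference, or 1.11² = 1.23 in information.

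**3. The worked knowledge design, 360 women.** Noncentrality = 0.172 / √(0.4815 × VIF / 180), where 0.4815 is the sum of the two binomial variances.

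| VIF | Noncentrality | Normal power | Power, 10 df |
|---|---|---|---|
| 1.26 (as stated) | 2.96 | 84% | 76% |
| 1.29 (360/12 = 30 per kebele) | 2.93 | 83% | 75% |

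**4. Knowledge at the adopted size.** 1,126 / 12 = 93.8 per kebele, so VIF = 1 + 92.8 × 0.01 = 1.93. Noncentrality = 0.172 / √(0.4815 × 1.93 / 563) = 4.24. Power with 10 df is 97% at 5% and 89% at 0.05/3.

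**5. Can 12 kebeles reach 80%?** Yes. With 424 women (35.3 per kebele, VIF 1.34) the noncentrality is 3.11 and power with 10 df is 80%.

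**6. MHSU at 1,126.** The inputs are not printed, so only a range can be given, on the assumption that the method of step 1 was used.
- Sized at exactly 80%: 71% at 5%, 50% at 0.05/3 (step 2).
- Sized with the continuity correction: for illustrative control rates of 34%, 48% and 74% (the survey rates in the same section) and VIF 1.26 or 1.93, the noncentrality is 2.88 to 2.92. Power is about 74-75% at 5% and at most about 54% at 0.05/3.
- If 1,126 also contains a 10% non-response allowance (assumed) that is not used up, the continuity-corrected power is about 78-79% at 5%.

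**The case against.** **The only outcome with printed inputs is not harmed.** The quoted calculation concerns knowledge, and its 360 is superseded by 1,126, where power is about 97%. This stands, and it confines the point to MHSU.

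**The MHSU figure is conditional.** A reader might infer that the trial's power for MHSU is 71%. The document does not support that as a fact, because the inputs behind 1,126 are absent. If the continuity correction used for 286 was used again, the figure is nearer 75%, and an unused non-response allowance would raise it further. Nor does 71% describe the quoted 286/360 calculation, which gives 75-76%.

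**Twelve kebeles are not in themselves too few.** A reader might infer that 80% at 5% cannot be reached with 12. Steps 4 and 5 show that it can. What falls short is the sizing method.

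**The 10-df test is not the planned analysis.** The Protocol plans GEE or multilevel models and t-tests on change from baseline. Baseline adjustment could move the noncentrality either way, and this part stands. But the choice of model does not create more randomised units. Any test that holds 5% with 12 randomised kebeles works on about 10 df.

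**Conclusion.** The concern holds in limited form. The Protocol's sizing method omits the small-cluster correction, and a design set at 80% by that method does not have 80% power at a two-sided 5% level.

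- **Worked 360-woman design:** about 75-76%.
- **Knowledge at 1,126:** about 97%, no practical consequence.
- **MHSU at 1,126:** about 71-75% at 5% and about 50-54% at the Bonferroni level, if sized by the same method, and higher with an unused non-response allowance.

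These figures rest on 6 equal kebeles per arm and, apart from the MHSU case sized at exactly 80%, on an ICC of 0.01 or a VIF of 1.26 or 1.93. Unequal kebeles would generally lower them. The MHSU range also rests on how 1,126 was obtained, which the document does not show.

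**What to change.** In Sample size calculation, recompute the power for objective 4 from its own inputs, using a t distribution with 10 df (number of kebeles minus 2) in place of the normal distribution. Then do one of the following:

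- restate the power, expected to be about 71-75% at 5%, with the figure at the 0.017 level beside it (expected about 50-54%); or
- keep 80% and state a detectable MHSU difference up to about 11% larger.

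Take the restated figure from the recalculation, not from the ranges given here. Qualify the statement that 12 clusters give adequate power as regards MHSU only; for knowledge at 1,126 women it can stand at the assumed ICC.

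The cost is one recalculation and a change of wording. No extra women are needed. The only downside is a less favourable stated power.

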
**Methods of selection of study respondents**

A multi-stage, purposive and stratified sampling technique will be used to select the study participants.

**Blinding**

Because of the nature of the study intervention neither research team members nor study respondents can be masked.

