**The inclusion and exclusion criteria**

All systematically selected WRA who gave live birth in the last 12 months, all purposely selected service providers and users, all pregnant mothers residing in the selected *kebeles* for at least for 6 months and have no plan to change residence during the implementation of an intervention, no psychiatric problems, capable of providing written informed consent, and voluntary to be visited by WDT facilitators, data collectors, and supervisors will be included for this study. Women who have a severe illness during the data collection period will be excluded from this study due to unable to communicate. Also, study subject who have a psychiatric disorder will be excluded due to that could affect participation and consent procedure. Similarly, women who experienced stillbirth and infant deaths will be excluded because the questions from this study are expected to re-memorize women the unfavorable pregnancy outcome they had faced. This may seriously affect maternal participation and genuine response. Midwives who have been serving in the maternal and child health case team for less than two years will be excluded. Due to this reason, these midwives have less experience and interaction with pregnant women and couldn’t provide in-depth information on perceptions, barriers, and facilitators of MHSU. Moreover, all WRA included in the quantitative study will be excluded because they have information during the quantitative study that may introduce information bias.

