**Data collection and quality control**

The study tools will be initially prepared in English, translated to Sidamic language, and reconverted back to English to retain its originality and consistency. The assessment will be conducted to evaluate the inconsistency among the 2 versions of the tools. It will be pre-tested on the 5% of sample size in kebeles that are not involved in the actual research area. Then, any inconsistency between the 2 versions will be amended accordingly. The training regarding tools will be provided for the data collectors and supervisors by the principal investigator for two days. During the training, attention will be given to the significance of the study, data collection procedure, objective, methods, and ethical issues. The quantitative and qualitative data collection will be conducted by employees of Hawassa University Health and Demographic Surveillance System (HDSS) and masters of public health experts. Two public health experts with RH will be carefully supervised the data collection method. The consistent checkup for incompleteness and non-consistency of the data will be made on a daily basis. Double data entry will be carried out. The incomplete, inconsistent, and invalid data will be distinguished correctly to acquire a high quality of data before, during, and after data entry. The corrections will be made based on the original data.

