**Intervention procedure**

WDA volunteers will be recruited by using the following selection criteria as able to read and write the Sidama language and are willing to do the intervention. Following recruitment, intensive training will be given for 1 week on the topics. One health education session consists of key messages on normal pregnancy, danger signs and complications during pregnancy, delivery, and the postpartum period, the practice of birth preparedness as well as complication readiness, and the benefits of MHSU. The other actions executed by WDA facilitators will be the motivating mother and their families for MHSU. One hour will be allocated for each session, from this 20 minutes will be allowed for the lecture which is moralistic in nature and the remaining 40 minutes will be allowed for raising questions and responses. After the session, some of the women will be selected to carry out role play which is basic to demonstrate the important messages and share experiences. This will be done to repeat the information provided to enable them to internalize the key message. The women will be also exposed to posters to reinforce the session message. The session will be conducted 2 times per month for six months. The follow-up will be conducted every month or more repeatedly if any potential problems indicated.

Interventional group (n= 563)

Control group (n= 563)

Included in to study (n = 1,126)

Randomization

Received CLHEI (n= 563)

Loss to follow up (n=)

Loss to follow-up (n=)

Analyzed at 6 months (n=)

Received routine intervention (n= 563)

Analyzed at 6 months (n=)

**Figure 1:** Flow Diagram for randomization of study participants in to intervention and control groups in Dale and Wonsho districts of Sidama region, Ethiopia.

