**The measurements**

**ANC utilization** is measured as a proportion of women who utilized ANC from skilled providers (HEWs, midwives, nurses, health officers, and doctors) at least once during the last pregnancy using a woman's self-report. However, different studies considered different figures of ANC visits being optimum. For instance, some researchers had fixed 2 ANC visits to be adequate. The WHO suggests at least 8 ANC visits throughout pregnancy while the first visit will be conducted before 16 weeks or within the first trimester. Therefore, standardization of the numbers of ANC use is required to assist the comparison of diverse or different studies. Accordingly, we considered utilization of ANC as a woman who has at least one ANC follow-up which is similar to EDHS. Besides, the time must be within the first trimester or before 16 weeks of gestation. Moreover, women must consume more than 90 iron-folic acids (IFA) tablets or syrup, receive at least one dose of tetanus toxoid injection, have a laboratory test result of syphilis, and blood group.

**Institutional delivery utilization** is measured as the proportion of women who utilized institutions (governmental health centers or hospitals, and/or private hospitals or clinics) for delivery in their last pregnancy using a woman’s self-report.

**PNC utilization** is measured as the proportion of women who utilized a PNC visit within 42 days after giving birth at least once using a woman’s self-report.

**Maternal knowledge regarding ODS** will be measured using the 30 questions during three phases namely antepartum (9 questions), intrapartum (12 questions), and postpartum (9 questions). The correct answers are assigned a score of 1, while incorrect answers are assigned a score of 0. Lastly, the total knowledge scores range from 0 to 30. The study respondents who spontaneously mention at least 3 ODS during each phase are classified as having “good knowledge” and those who are not able to spontaneously mention 2 or fewer ODS have “poor knowledge”.

**Spontaneous knowledge** is defined as the knowledge of study participants who can name or call an ODS without being read the name of that sign by data collectors. Merely true ODS spontaneously mentioned by study participants will be recorded during the interview.

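### The Blinding section rules out masking for the whole research team, for a reason that covers only participants and session facilitators; endline interviewers and the analyst could be at least partly masked

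*Protocol*

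**What the plan says.** The Blinding section of the protocol is one sentence. It gives the character of the intervention as its reason and concludes that "neither research team members nor study respondents can be masked". It makes no distinction between those who deliver the education, those who measure outcomes and those who analyse them.

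Three other sections describe who does what.

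- **Delivery.** Under Intervention procedure, "WDA volunteers will be recruited by using the following selection criteria as able to read and write the Sidama language". These volunteers are trained for a week and run the sessions twice a month for six months. The same section plans follow-up at least monthly, without naming who does it.
- **Measurement.** Under Data collection and quality control, data collection "will be conducted by employees of Hawassa University Health and Demographic Surveillance System (HDSS) and masters of public health experts".
- **Roles listed apart.** The inclusion criteria require women to be "voluntary to be visited by WDT facilitators, data collectors, and supervisors".

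On the outcomes, The measurements section takes service use from the woman's own account. For antenatal care the wording is "at least once during the last pregnancy using a woman's self-report", and institutional delivery and postnatal care are likewise self-reported. Birth preparedness rests on her answers about five components. For knowledge of obstetric danger signs, "Merely true ODS spontaneously mentioned by study participants will be recorded during the interview".

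**The concern.** Attending or leading an education session makes it impossible to mask the woman or the facilitator. It does not make it impossible to withhold a kebele's allocation from someone who arrives later with a questionnaire, or from someone who receives a data file with coded arms. The protocol's reason is therefore narrower than its conclusion. This is a stated rule, not a detail left for a later document to settle.

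What is at stake is arm-dependent measurement. An interviewer who knows the arm may prompt a little more, or credit a vague answer more readily, in one arm than in the other. Such a shift adds directly to the estimated difference. Randomisation does not remove it, and a larger sample only measures the biased difference more precisely.

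**Working it through.** The point rests on reading the sections together. The protocol gives no figure for it, so there is none to reproduce.

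**1. Whom does the stated reason cover?** Participants: yes. Facilitators: yes. Data collectors: only if they take part in delivery. Analyst: no.

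**2. Do data collectors take part in delivery?** No section gives them a part. Delivery is assigned to recruited volunteers and measurement to surveillance-site employees and master's-level public health experts. The inclusion criteria name facilitators and data collectors separately (taking WDT and WDA facilitators to be the same people). This is an inference from role descriptions, and the unassigned monthly follow-up leaves a gap in it.

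**3. How far can an interviewer influence each outcome?**

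| Outcome | Source | Interviewer's scope |
|---|---|---|
| Antenatal care, institutional delivery, postnatal care | Woman's self-report, yes/no | Smaller: wording and probing |
| Birth preparedness | Her answers on five components | Smaller |
| Danger-sign knowledge | Spoken answers, scored 0 to 30 | Larger: decides whether each sign was true and unprompted |

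No record check is described for any of them. For knowledge, the good-knowledge class needs three signs per phase, so crediting one borderline sign can change a woman's class.

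**4. Do the stated safeguards cover it?** The Bias section lists standardisation, training and randomisation, but no masking of interviewers. Interviewer training includes the study objective, so interviewers know what the trial hopes to show. Double entry and correction against the original record cannot detect differential crediting, because that record is already the interviewer's judgement.

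**5. Sensitivity illustration only.** The size of any shift is assumed, because the documents give none. Take no true effect, 45.7% with knowledge in both arms (the control value in the sample size section), 563 per arm, 12 kebeles and ICC 0.01.

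- Mean cluster size: 1,126/12 = 93.8.
- Design effect: 1 + (93.8 − 1) × 0.01 = 1.93.
- Effective size per arm: 563/1.93 ≈ 292.
- SE = √[p(1−p)/292 + q(1−q)/292], where p = 0.457 and q = p + shift. The two-sided rejection probability is then taken from the normal distribution.

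| Assumed shift in one arm | Rejection at 0.05 | Rejection at 0.05/3 = 0.017 |
|---|---|---|
| 0 points | 5% | 1.7% |
| 2 points | 8% | 3% |
| 5 points | 23% | 12% |
| 10 points | 68% | 51% |

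The table shows how a given shift would act. It does not say that any such shift will occur. It also uses the two-class version of knowledge, whereas the Statistical data analysis section compares mean changes in score.

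**The case against.** The best case for leaving the section alone has four parts.

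- **Masking may fail in the field.** Whole kebeles are allocated, only 12 are used, and intervention kebeles have twice-monthly sessions and posters for six months. One remark can reveal the arm for every woman in a kebele. This stands: masking would be partial. A reader might infer that unmasked assessment is wholly avoidable, and the documents do not support that. Partial masking of interviewers is still better than none, and coded arms for the analyst do not depend on what happens in the field.
- **Separation of roles is not stated.** This also stands. A reader might take it as settled that data collectors have no part in delivery. The protocol only implies it, and they might be the ones who carry out the monthly follow-up. The remedy is to state the separation.
- **Interviewer discretion is already limited.** The questionnaire is structured, validated and pre-tested. Interviewers are trained and supervised, with daily checks, and the rule to record only spontaneous mentions is itself a guard against prompting. These measures reduce discretion, but they do not stop an interviewer who knows the arm from applying the rule differently by arm.
- **The mechanism fits some outcomes poorly.** A reader might call every outcome purely self-reported and equally exposed. Knowledge is scored by the interviewer and is the most exposed. Yes/no service use leaves less room, and its main threat is the women's own reporting, which masking interviewers does not touch.

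**Conclusion.** The concern holds in a limited form. The blanket statement in the Blinding section is not supported by the reason it gives: that reason covers participants and WDA facilitators only. On the protocol's own role descriptions, endline interviewers could be kept unaware of allocation at least in part, and the analyst could work with coded arms. The case is strongest for the danger-sign knowledge score.

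The size of the bias cannot be derived from the documents. A reader might set an assumed 5-point shift against the planning difference of 62.9 − 45.7 = 17.2 points and conclude that 5/17.2 = 29% of the planned effect could be spurious. That is not supported. The 5 points are invented, the 17.2 points are a before-after difference on a threshold measure from another study, and the planned analysis compares mean score changes.

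The conclusion assumes that data collectors are, or can be made, separate from delivery and follow-up. It is a low-cost improvement to a stated rule, and one that cannot be made once endline data are collected.

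**What to change.** Limit the Blinding statement to participants and WDA facilitators, and add that:

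- endline data collectors will not be told kebele allocation, and will take no part in sessions or in the monthly follow-up;
- participant lists given to them carry no arm labels;
- any questions on session exposure come last in the questionnaire;
- the analyst works with coded arms until the main analysis is final;
- interviewers record at the end whether they learned the arm.

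The cost is changed fieldwork instructions and a coded data file. The same staff and sample serve, provided that someone other than the endline data collectors does the monthly follow-up. Masking will still be partial, since women's remarks or posters may reveal a kebele's arm. The change reduces interviewer bias but leaves the women's own reporting bias, which the report should acknowledge.
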